### Procedures

#### Recruitment

The flowchart displayed in Fig. 1 summarizes the recruitment procedure. Patients attending health clinics for depression in the catchment area will be contacted by telephone and invited to participate in the study. Those who accept will be asked to answer a few screening questions on the telephone and, if they meet the inclusion criteria, will be invited for the primary assessment at their usual health clinics. This first assessment will involve further information on the study, clarification of any doubts or questions that prospective participants may have, and signing of the informed consent forms. After this, final screening measures that can only be done face-to-face will be administered. If eligible, participants will be assigned alphanumeric participant codes, and baseline evaluations will be conducted.

**Fig. 1 Fig1:**
[figure not shown]
Flowchart of study design and participant flow, from enrolment to final follow-up

#### Randomisation

Once the family is fully enrolled and baseline evaluations are completed, the family will be randomised to either the intervention arm or a waiting-list group by a collaborator who will be blind to all evaluation outcomes and will conceal the allocation sequence until the intervention is assigned. The randomisation will be done with the use of a random number generator and will be stratified by health centre catchment areas. The use of block randomisation means that the intervention can be delivered in a staggered manner, with some participants beginning the intervention while further recruitment continues.

#### Blinding

The primary outcomes involve intervention-specific questions, so blinding becomes impossible. For the secondary outcomes, however, evaluators will be blind to the treatment allocation as well as those carrying out the statistical analyses. The randomisation and statistical analysis will be carried out by someone unconnected to the recruitment process.

#### Intervention arm: Family Talk PIP for Depression

A manualized intervention will be carried out, designed by Beardslee and his team. This is a preventive intervention programme for depression aimed at families in which one or both parents have depression. It is family-centred and focused on the strengths of the family. Based on cognitive, narrative and systemic therapy, Family Talk aims to strengthen family relationships, functioning and communication. It is divided into seven modules that will be delivered weekly (plus follow-up):Module 1: Depression and familyModule 2: Psychoeducation about depressionModule 3: The perspectives of children on their parents’ depressionModule 4: Skills developmentModule 5: Preparing for family meetingModule 6: Family meetingModule 7: Review and future planningFollow-up

Each module is a 60- to 90-minute meeting wherein parents learn about depression, discuss their experiences and develop coping skills.

#### Waiting-list control group

Families assigned to the control group will carry on with their treatment as usual; this will most likely be treatment for depression in parents. Additionally, they will be in regular contact with the research team, imitating the frequency of contact in the intervention group. At the end of the study, these families will also benefit from the intervention.

#### Follow-up

All families will be assessed at the same time points after being included in the study. For families in the intervention group, this translates into the following five phases: pre-intervention, post-intervention, 3 months post-intervention, 6 months post-intervention and 9 months post-intervention. Since the intervention should last around 2 months, follow-up points for families in the control group would translate into the following five stages: baseline and 2 months, 5 months, 8 months and 11 months after baseline.

### Data analysis

Data will be collected by the trained therapists and handed to the trial coordinator, who will tabulate and safely store all forms. Once participant data are coded and entered into the database, 20 % of it will be checked by a different researcher to ensure all data entry was correct.

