#### Qualitative measures

Acceptability will be measured via qualitative feedback forms after each session. These forms will include questions on the participants’ thoughts and opinions about the intervention content and its delivery. They will include items such as, “How relevant to you and your family’s issues was this module?”, “How satisfied were you with today’s session?”, and “In your opinion, is there anything that prevented the session from suitably taking place?” The feedback obtained from this questionnaire will be used to continuously optimise the intervention. Furthermore, at the end of the intervention, focus groups will be created for families and therapists. Forms designed to determine which components of the intervention are covered in each session will be completed to ascertain the integrity of the intervention and adherence to the manual. To further examine the acceptability of the intervention and adherence to the manual, 20 % of the total number of sessions in the studies will be videotaped for those families who give their consent.

The feasibility of this pilot study requires that the intervention be effectively carried out with an adequate number of families and within the delineated time. The feasibility of the recruitment process will include the number of families sampled and contacted, those families who accept, the number of families who complete the intervention and reasons for ineligibility, and non-participation or early withdrawal from intervention. The feasibility of the intervention will include the number of sessions attended, time taken to complete questionnaires (burden of questionnaire completion), items left blank on questionnaires, follow-up rates and dropout. The number of therapists available and how many families they manage to visit per week will also be noted. As it is important to evaluate whether the administration and assignation of resources is effective, supervisors at health centres will also be interviewed.

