#### Quantitative measures

The following quantitative measures will be used:M.I.N.I.: The Mini International Neuropsychiatric Interview (M.I.N.I.) version 5.0 [46] is a brief structured diagnostic interview developed in 1990 by doctors and psychiatrists in the United States and Europe. With a delivery time of approximately 15 minutes, the M.I.N.I. 5.0 is a diagnostic tool for psychiatric disorders based on the *Diagnostic and Statistical Manual of Mental Disorders, Fourth Edition* (DSM-IV), and the International Classification of Diseases, Tenth Revision.BDI-II: The BDI-II is a self-assessed multiple-choice scale consisting of 21 questions. It is one of the most widely used instruments in the world that measures the severity of depression. It is designed for people older than 13 years of age and consists of items that measure depressive symptoms, hopelessness, irritability, guilt and physical symptoms.E2P: The Positive Parenting Scale (E2P) is a self-administered 54-item questionnaire on parental skills which covers four subcategories: bond, development, protection and self-reflection.FACES-II: This is the second version of FACES, a self-administered scale measuring cohesion and adaptability in the family. There are 50 items, 25 of which are intended to explore the dimension of cohesion and the remaining 25 adaptability.MINI-Kid [47]: The Mini International Neuropsychiatric Interview for Children and Adolescents (MINI-Kid) is the children’s version of the M.I.N.I. The structure is identical, but the questions are modified to facilitate the understanding of children.CDI: The Children’s Depression Inventory assesses depressive symptoms and provides a total score for depression in children. It may be self-administered by the children, but in this investigation it will be administered by an evaluator. It consists of 27 items, each consisting of 3 statements, and measures 2 dimensions: dysphoria (depressed mood, sadness, worry, and so forth) and negative self-esteem (judgments of inefficiency, ugliness, evil, and so forth).CBCL: The Child Behaviour Checklist scale is completed by parents to detect emotional and behaviour problems in children and adolescents. It consists of 113 questions, scored on a 3-point Likert scale (0 = absent, 1 = happens sometimes, 2 = often occurs). This scale provides information on the following syndromes: anxiety, depression, somatic complaints, social problems, thought problems, attention problems, and rebellious and aggressive behaviour. Also, it has six scales based on DSM-IV diagnostic categories: emotional problems, anxiety, somatic problems, attention-deficit/hyperactivity disorder, oppositional defiant problems and behaviour problems.School Resilience Scale (ERE): This scale contains 27 items for children between the ages of 9 and 14 years. The ERE measures the level of overall resilience of children and pre-adolescents in three main areas (I am, I can and I have) subdivided into five dimensions: self-identity, network models, learning generativity, internal resources and external resources.WISC-III: Two subscales of the WISC-III will be administered to measure processing speed. In the coding test, there is a series of simple forms (coding A) or numbers (coding B), each of which has a corresponding code, and the child is asked to draw the symbol under its corresponding form or number according to a key. In the symbol search test, the child is asked to decide whether target symbols appear in a row of symbols.

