#### Therapist recruitment

The people recruited to carry out the intervention will be psychologists and social workers in the different health centres as well as in schools within this catchment area. They will undergo a total of 9 h of training with a final assessment as an indicator of their abilities. It is expected that 20–25 people will be successfully trained in the intervention.

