### Strengths

This trial was met with a lot of support from the local authorities who wish to implement it as a usual intervention for children at risk for depression. Some of the strengths of this study are that the intervention will be carried out by trained psychologists and social workers who have experience working with this population. They will also be constantly supervised as an added support measure.

The fact that the intervention will be carried out at the participants’ homes is a major strength. This setting will provide the therapists with the ability to use the patient’s own environment and modify it for the family’s benefit. It will also provide the researchers with valuable qualitative information regarding whether the intervention works best in different home environments and what components of these would facilitate intervention delivery. This makes for a more personalised intervention, better fitted for each family’s needs.

Having a home-delivered intervention requires taking into account several safety challenges. Fortunately, the collaborating health centres already have the safety procedures and infrastructure set in place for home visits. Their workers therefore are fully aware of all safety procedures to be taken into account when delivering interventions in this setting.

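### Therapists who deliver the intervention are named as data collectors, which conflicts with the stated blinding of evaluators for the secondary outcomes

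*Protocol article*

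**What the plan says.** All references are to the protocol article.

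- **Data analysis**, opening paragraph: "Data will be collected by the trained therapists and handed to the trial coordinator, who will tabulate and safely store all forms". The sentence makes no exception by type of form, arm or time point. It stands above both the qualitative and the quantitative analysis subsections.
- **Therapist recruitment**: "The people recruited to carry out the intervention will be psychologists and social workers in the different health centres", and also in schools of the area. The same section expects 20–25 such people, who "people will be successfully trained in the intervention" after 9 hours of training.
- **Strengths**: "the intervention will be carried out by trained psychologists and social workers who have experience working with this population".
- **Blinding**: the primary outcomes are said to be impossible to blind. Then: "For the secondary outcomes, however, evaluators will be blind to the treatment allocation", and the analysts are to be blind as well.
- **Design**: the quantitative part is labelled a single-blind randomised trial.
- **Quantitative measures**: children could complete the CDI themselves, but "in this investigation it will be administered by an evaluator".
- **Qualitative measures**: acceptability is measured by feedback forms after every session, with items such as "How satisfied were you with today’s session".

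**The concern.** A person who has run home sessions with a family knows that the family is in the intervention arm. If that person also collects the outcome data, the evaluator of that family is not blind.

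The measure most exposed is the CDI. It is put to children aged 6 to 12 by an adult, and it is the listed measure of child depressive symptoms. Those symptoms are the subject of the first hypothesis and of the sample size calculation. The pilot is also meant to inform a definitive trial and to provide parameters for its sample size, so a distorted contrast between arms could carry forward.

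A second and separate matter is acceptability. A family that hands a satisfaction rating to the therapist who has just led the session may answer more kindly than it otherwise would.

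**Working it through.** No disputed figure is involved, so the check sets the statements side by side.

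**Step 1: who are the trained therapists?** Therapist recruitment describes the people recruited to deliver the programme and says what they are trained in. Strengths repeats that trained psychologists and social workers deliver it. The article describes no other group as trained therapists, so the collectors named in Data analysis are the deliverers.

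**Step 2: what do they know?** The intervention is seven weekly home modules, and the control is a waiting list with usual treatment. Delivering a module reveals the arm.

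**Step 3: can both statements be followed?**

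| If therapists collect the secondary outcomes | If they do not |
|---|---|
| The evaluator-blinding statement and the single-blind label fail for families assessed by staff who treat them | The Data analysis sentence is wrong as written |

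Nothing in the article settles which applies. Blinding separates randomisation and statistical analysis from recruitment, but no section separates evaluators from therapists.

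**Step 4: which measures are exposed?**

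- CDI: expressly administered by an evaluator.
- WISC-III coding and symbol search: described as administered; the administrator is not named.
- BDI-II, E2P and FACES-II are self-administered or self-assessed, and the CBCL is completed by parents. The collector's influence there is at most indirect.
- School Resilience Scale: the mode of completion is not stated, so it is not counted.

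**Step 5: which assessments are exposed?** Follow-up lists five: baseline and 2, 5, 8 and 11 months. Randomisation says that baseline evaluations are completed before allocation, so there is no allocation to know at that point. Exposed assessments: 5 − 1 = 4.

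**Step 6: link to the plan's only design figure.** The sample size section expects 0.33 of control and 0.05 of intervention children to develop depressive symptoms, and asks for 32 per arm. Significance level and power are not stated; assume two-sided 0.05 and 0.80. With unpooled variance:

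n = (1.96 + 0.84)² × (0.33 × 0.67 + 0.05 × 0.95) / 0.28² = 7.84 × 0.2686 / 0.0784 = 26.9, rounded up to 27.

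27 / (1 − 0.15) = 31.8, rounded up to 32.

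The stated figure is reproduced. The point does not depend on it; it shows only that the trial was sized on child depressive symptoms, the domain that the CDI measures.

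**The case against.** The best defence is that the article uses two words consistently: *evaluator* under Blinding and Quantitative measures, and *therapist* under Therapist recruitment and Data analysis. Two readings would then reconcile the text. Therapists may hand in only the session and integrity forms, which fits the reference to storing forms. Alternatively, with 20–25 trained people, a therapist may assess only families treated by someone else. Either is plausible, and an article need not list who completes every form. But neither reading is stated. The difficulty is also more than missing detail: one unqualified rule conflicts with another. The defence does show that loss of blinding is not established, only that the text as written would produce it.

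Other objections stand and limit the point:

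- A reader might infer that the CDI result would be biased in favour of the intervention by some fraction of a standard deviation. The document supports neither size nor direction. Its Background reports increased recognition of depression in children after the programme, so an informed assessor could also record more symptoms in the intervention arm.
- A reader might add the MINI-Kid. Its only stated use is to exclude depressed children, which happens before randomisation, and it is not a listed secondary outcome.
- A reader might say that the parent-completed scales break the blind as well. The protocol claims blinding only for evaluators and analysts, never for parents, and parents in a waiting-list trial necessarily know their arm. No statement is contradicted.
- For acceptability, the article already concedes that blinding is impossible. It also plans focus groups and video recording of 20 % of sessions, with two researchers coding interview and video data independently. These sources partly offset kind answers on the forms. That the form returns to the treating therapist is the natural reading of the Data analysis sentence, but Qualitative measures does not say so.

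**Conclusion.** The conflict is real. The data-collection sentence cannot be applied as written while keeping the evaluator-blinding statement and the single-blind label. If it is followed, the CDI and the WISC-III subtests are at risk of detection bias at the four assessments after randomisation, with size and direction unknown. The acceptability ratings are at risk of socially desirable answers, which is a measurement weakness and not a breach of a blinding claim.

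The conclusion rests on two things: that trained therapists means those who deliver the programme, which two sections support, and that the word data covers the outcome measures, since no exclusion is given. It does not show that blinding has been lost in practice. The blinding conflict touches only secondary outcomes of a pilot described as mainly exploratory. It still needs correction, because staff who follow the text literally would undo a protection that the article claims.

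**What to change.** Rewrite the opening of Data analysis to say who collects what:

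1. Secondary outcomes at the four post-randomisation assessments are collected by the evaluators already mentioned under Quantitative measures and Blinding. They do not deliver the intervention to the family they assess and do not know its allocation.
2. Therapists hand in only session-content and adherence forms.
3. Families return satisfaction forms to the trial coordinator without passing them through the treating therapist.

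If blinded evaluators are not in fact available, withdraw the evaluator-blinding statement under Blinding and the single-blind label under Design.

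The cost is a change of wording and some reallocation of assessment tasks among staff. The article commits to blinded evaluators but does not describe their staffing, so the sponsor should confirm that they can cover all four assessments.

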#### Qualitative data analysis

For the interview and video data analysis, two researchers will independently code the data and key themes of the interviews will be identified. Any differences encountered by the researchers will be discussed and resolved between them. Feedback from satisfaction surveys will be used to improve the delivery and content of the intervention.

#### Quantitative data analysis

Data presentation and results will be carried out according to Consolidated Standards of Reporting Trials (CONSORT) guidelines for RCTs. An ‘intention-to-treat’ basis will be used for the analysis of all participants allocated to the study groups. Initially, a descriptive analysis of the sample will be performed. The variables will be summarized at the different time points to evaluate any changes. To evaluate the changes produced by the intervention in the different treatment groups, and on variables of a continuous nature, two-way analysis of variance will be conducted. The independent variables will be ‘time’ (pre- vs. post-treatment) and ‘group’ (intervention group vs. control group). Other exploratory analyses will be carried out to see which variables have an effect on the outcome. Logistic regression analyses will be used to adjust for predictor variables of a dichotomous outcome, such as presence or absence of psychopathology, whereas linear regression analyses will be conducted to determine the effects of predictors on the continuous variables, such as family functioning. A sensitivity analysis will be conducted to investigate the potential effects of incomplete or missing data.

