#### Sample size calculation

Despite the fact that a power calculation is not fully appropriate for a feasibility study [48], we have estimated a suitable number of children for this study. We expect that the proportion of children who will develop depressive symptoms within 1 year in the waiting-list control group will be 0.33, compared with 0.05 for those children in the intervention arm. For a loss to follow-up calculated at 15 % and in a two-sided contrast analysis, 32 children will be required per arm and 64 children in total. Despite there being evidence to support a one-sided analysis for this case, since we assume the intervention will not cause harm, we will carry out a two-sided analysis as is common in RCTs. This number is adequate according to recommendations for feasibility studies which propose a minimum of 30 participants per arm to estimate parameters for future sample size calculations [49, 50].

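### The only named group comparison for continuous outcomes stops at about 2 months, so the 5-, 8- and 11-month scores have no specified test, and its error structure is not stated

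*Protocol article*

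**What the plan says.** The Quantitative data analysis section of the Protocol article names one method for comparing the arms on continuous outcomes: "on variables of a continuous nature, two-way analysis of variance will be conducted". It gives the two factors, time and group, with levels "pre- vs. post-treatment) and ‘group’ (intervention group vs. control group". Of the visits in general it says: "The variables will be summarized at the different time points to evaluate any changes". Logistic and linear regressions follow as further exploratory analyses, with no visit and no predictors named. A sensitivity analysis for missing data is planned.

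The Follow-up section puts all families on one schedule, expressed for controls as "baseline and 2 months, 5 months, 8 months and 11 months after baseline". The post-treatment visit is the 2-month one: "Since the intervention should last around 2 months".

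Under Secondary outcomes, the child hypothesis is that depressive and internalising symptoms will not increase relative to the waiting-list arm. Under Randomisation, allocation "will be stratified by health centre catchment areas".

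**The concern.** Two things are fixed badly.

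First, the named test uses two of five assessments. A claim that symptoms do not rise is a claim about what happens over time, yet the specified comparison is made as the intervention finishes. The visits that could show whether an early difference lasts, or whether a later one emerges, are collected from every family and then only described.

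Second, the same child supplies both the pre and the post score. A two-way ANOVA with time and group as factors can be fitted with one error term, treating those scores as unrelated, or as a mixed ANOVA with a subject term. The text does not say which, and the two give very different tests. Under either, baseline is used less efficiently than as a covariate, and the stratification factor is absent.

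At stake is the usefulness of the pilot's effect estimates for the definitive trial: the plan specifies no 11-month group effect with its uncertainty.

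**Working it through.** **Visits used.** There are four follow-ups (2, 5, 8 and 11 months). The ANOVA uses the first, so 4 − 1 = 3 receive descriptive summaries only.

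**Evaluable sample.** Under Sample size calculation, the article gives 0.33 against 0.05, 15% loss, a two-sided test and 32 children per arm. Alpha and power are not stated; I assume 5% and 80%. With unpooled variances:

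n = (1.960 + 0.842)² × (0.33×0.67 + 0.05×0.95) / 0.28² = 26.9, rounded up to 27 per arm; 27 / 0.85 = 31.8, rounded up to 32.

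The plan's figure reproduces, so the sample size is not in question. I use 27 evaluable per arm.

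**Assumptions.** The article gives no pre/post correlation (ρ) and no standardised effect. I assume bivariate normal scores with SD 1 at both visits, ρ from 0.3 to 0.7, and an effect of 0.5 SD at the post visit.

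**Variance of the estimated effect:**
- Group-by-time interaction (difference in mean change): true variance 4(1 − ρ)/n.
- The same contrast under independent errors: the model takes the variance as 4/n, too large by a factor 1/(1 − ρ).
- ANCOVA on baseline: about 2(1 − ρ²)/n, which is (1 + ρ)/2 of the change-score variance. That is 0.75 at ρ = 0.5 and 0.80 at ρ = 0.6.

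**Type I error of the interaction under independent errors.** There are 4 × (27 − 1) = 104 degrees of freedom, so the critical value is 1.983. The actual rejection rate is about 2 × [1 − Φ(1.983/√(1 − ρ))]:
- ρ = 0.5: 1.983/0.707 = 2.80, giving 0.5%.
- ρ = 0.6: 1.983/0.632 = 3.14, giving 0.17%, or about 0.2%.

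**Simulation** (at least 40,000 trials per setting, 27 per arm, nominal 5%):

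| ρ | Type I, independent-errors interaction | Power, independent errors | Power, mixed ANOVA | Power, ANCOVA |
|---|---|---|---|---|
| 0.3 | 2.0% | 21% | 33% | 47% |
| 0.5 | 0.5% | 17% | 44% | 54% |
| 0.6 | about 0.2% | 15% | 52% | about 60% |
| 0.7 | 0.05% | 12% | 64% | 70% |

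Mixed ANOVA and ANCOVA keep type I error at about 5% throughout. So the independent-errors version would lose most of the power, and the mixed version would lose about 8 to 10 percentage points against ANCOVA at ρ = 0.5 to 0.6.

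**The case against.** The strongest reply is that the ANOVA is probably a mixed one. Its stated purpose is to assess change, which points to the group-by-time interaction, and calling time and group independent variables is ordinary language for model factors. A reader might infer that the plan ignores within-child correlation and that its error rates are therefore wrong. The document does not support that: it leaves the structure open, and a mixed ANOVA has correct type I error. The main effect of group would be inflated under independent errors (10.9% at ρ = 0.5), but it is not the effect the section sets out to test. What stands is that the wording admits both versions and should name one.

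Other strong readings also fail:
- **Baseline is left out.** It is the pre level of time, and the interaction is a comparison of change scores. It is used inefficiently, not omitted.
- **Leaving out health centre inflates false positives.** It usually costs some power and makes the test slightly conservative. The exploratory regressions do not rule centre or baseline out.
- **The test contradicts the sample size horizon.** The rates concern "children who will develop depressive symptoms within 1 year", a binary outcome, which would fall under logistic regression with no visit named. They show that the planners think beyond 2 months, but they do not set the time point for continuous scales.
- **The analysis breaches intention to treat.** No complete-case rule is stated, and a missing-data sensitivity analysis is planned.
- **The SDs for the definitive trial are compromised.** They can come from the descriptive summaries at every visit.

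It is also fair that the primary outcomes are acceptability and feasibility, that all scales are secondary, and that no test is called the main one. That limits severity. It does not answer the point about later visits, because the choice of pre against post is stated in the text rather than left to another document.

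**Conclusion.** The point holds in a limited form. On any reading, the one named group comparison for continuous outcomes ends at about 2 months, and three of four follow-ups have no specified between-group analysis, although the child hypothesis is a preventive one. Separately, the error structure is unspecified. At ρ = 0.5 to 0.6 the choice decides between 15 to 17% and 44 to 52% power for a 0.5 SD effect, and baseline adjustment would raise the latter to 54 to 60%. These figures rest on 27 evaluable per arm, normal scores and the assumed correlation and effect size; the first conclusion needs none of them. Severity is moderate: secondary outcomes, an exploratory pilot, and a remedy that uses data already scheduled for collection.

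**What to change.** Replace the two-way ANOVA with a linear mixed model on the 2-, 5-, 8- and 11-month scores. Fixed effects: arm, visit, arm-by-visit, baseline score and health centre. Random effect: child (for parent-reported scales of the parent's own state, the parent), plus family if siblings are enrolled. Report the arm difference with a 95% CI at every visit, including 11 months.

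This settles the error structure, uses baseline as a covariate, reflects the stratified randomisation, and keeps children who miss the 2-month visit but are seen later, which serves the stated intention-to-treat basis.

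The cost is a revised paragraph, slightly more programming and a few degrees of freedom for centre (five centres, so 5 − 1 = 4). No new data are needed. If the ANOVA is kept for any reason, the text should at least say that it is a repeated-measures analysis and state how the 5-, 8- and 11-month scores enter the comparison of arms.
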